### Sample size

The power calculation is based on data from a recent international study on individual placement and support, which is an evidence-based reintegration model that is also used for people with MHI who want to have regular employment [45] and has the same primary outcome measure, i.e. obtaining employment. In this study, the average percentage employment was 50% in the intervention group and 20% in the control group [45]. Considering 50% and 20% as possible percentages, 36 unemployed people are needed in each group to find a statistically significant difference (with a 5% significance level and power of 80%): 47 participants per group would be needed for power of 90%. However, in this study any cluster effects and the expected dropout of participants over the four measurements must be considered. Considering a dropout rate of approximately 40% because of the vulnerable population, a safe assumption is to have 75 participants per group, which means a total of 150 participants.

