### Study design

The DECIDES study is a longitudinal, two-armed, clustered RCT of unemployed people with MHI who receive social benefits and/or reintegration support from Dutch municipalities. In this RCT the effects of an intervention that consists of a decision aid for unemployed people (CORAL.NL) and training for employment specialists who guide them in their job-seeking process are evaluated. Randomization took place at organization level (see Fig. 1). Participants are assessed at baseline (T0), and at 3 months (T1), 6 months (T2) and 12 months (T3). In addition, data on employment history (e.g. having employment, income, working hours per week and employment characteristics such as contract and employment type) and social benefits (e.g. having social benefits, duration of social benefits and the amount of social benefits) are extracted anonymously from the registration systems of the municipalities and Statistics Netherlands from T0 to T3 in participants who give consent for this. Collecting data from registration systems is more reliable and is less burdensome for participants. Participation in the study is voluntary and all participants sign an informed consent form for participation, and provide separate consent for the retrieval of their personal data from Statistics Netherlands. Measurements take place in one-by-one appointments with a researcher on the project. Participants can fill out the questionnaire digitally or by paper and pencil. If necessary, the researcher gives support by filling out the questionnaire, e.g. by explaining or reading out loud the questions for illiterate participants. Participants were stimulated to complete follow up by handing out a financial remuneration of 10 euros and by asking several contact options (mobile phone, email) to maintain contact during the participation period. If participants give consent to collect their data from Statistics Netherlands these data will also be collected if they discontinue filling out the questionnaires.

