### Setting

In the Netherlands, people older than 18 years are entitled to social benefits if they have insufficient income or capital and are unable to make use of another provision or benefits, such as disability benefits. In order to receive social benefits, (re)integration obligations must be met, such as cooperating in the support that the municipality offers aimed at entering the job market or returning to existing employment. This support is offered per municipality, and is often organized differently per municipality. Regarding disabilities and employment, the Netherlands has confirmed the U.N. Convention on the Rights of Persons with Disabilities [28] and has its own Disability Discrimination Act. The convention and act indicate that organizations and employers need to ensure that employees with disabilities have access to reasonable accommodations at work [29]. This anti-discrimination legislation may influence the employment status of people with disabilities in various ways. Employees do not have legal obligations to inform the employer about a disability as long as the impairment does not result in any endangerments at the workplace. However, disclosure of a health problem may be necessary for access to accommodations whereby this only can be implemented if the employer has knowledge of the disability, especially when natural support in the workplace is not available. Organizations commonly perceive such legislation and policies as a burden, e.g. because Dutch employers must pay at least 70% of the salary of a sick employee during the first 2 years of sickness absence [30]. This in fact might lead employers to try to avoid hiring a person with a disability [29].

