### Procedure

#### Randomization of employment specialists (ES)

All 72 participating employment specialists were recruited between November 2017 and March 2018 from eight participating organizations. Two researchers presented the study during meetings at the local organizations, provided written information about the study and provided a registration form and informed consent form. After including all employment specialists, the organizations were randomly allocated to either the intervention or control condition, using SPSS software. Cluster randomization was chosen, as individual randomization would have higher risk of contamination between the intervention and control group, because employment specialists within organizations work together on a daily basis. Due to the nature of the intervention, neither the employment specialists nor the researchers can be masked to the allocation to the conditions.

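### The sample size says cluster effects must be considered but allows no stated amount for them, so 75 per arm is not shown to be safe with eight randomised organisations

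*Protocol article*

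**What the plan says.** The Sample size section takes its event rates from an earlier study of supported employment, in which "the average percentage employment was 50% in the intervention group and 20% in the control group". From these it states that "36 unemployed people are needed in each group to find a statistically significant difference" at a 5% level and 80% power, and that 47 per group would be needed for 90%. It continues: "However, in this study any cluster effects and the expected dropout of participants over the four measurements must be considered". The next and last sentence of the section cites a dropout of roughly 40% and ends: "a safe assumption is to have 75 participants per group, which means a total of 150 participants". No ICC, cluster size or design effect appears.

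Three other places bear on this:

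- **Randomization of employment specialists:** the unit allocated is the organisation, and there are eight. "All 72 participating employment specialists were recruited between November 2017 and March 2018 from eight participating organizations".
- **Setting:** on job-seeking support, "This support is offered per municipality, and is often organized differently per municipality".
- **Study design:** on the employment register, "If participants give consent to collect their data from Statistics Netherlands these data will also be collected if they discontinue filling out the questionnaires". Consent for this is separate from consent to take part.

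The Statistical analysis section plans a longitudinal multilevel analysis and does not name its levels.

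**The concern.** The section names two things that must raise the sample size, quantifies one, and calls the total safe. The other is clustering. The document itself gives reason to expect it: municipalities run their services differently, and organisations were randomised because specialists within them work together. With only eight organisations, the number of clusters limits power as well as the number of participants.

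Obtaining employment is the outcome used for powering and the subject of the first research question. A reader who meets a non-significant employment result will judge it against the 80% and 90% in this section. Those figures describe individual randomisation, not the design being run.

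**Working it through.** **Inputs from the protocol article.** Employment 50% against 20%; 5% level; 36 and 47 per arm; dropout 40%; 75 per arm; eight organisations.

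**Assumptions, because the article does not give them.** Two-sided test; four organisations per arm; equal organisation sizes; ICC from 0 to 0.10.

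**1. The plan's own figures.** Unpooled normal formula without continuity correction:

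n = (z₁ + z₂)² × [p₁(1 − p₁) + p₂(1 − p₂)] / (p₁ − p₂)², with 0.25 + 0.16 = 0.41 and 0.30² = 0.09.

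- 80% power: (1.960 + 0.842)² × 0.41 / 0.09 = 35.8, so 36.
- 90% power: (1.960 + 1.282)² × 0.41 / 0.09 = 47.9, so 48, or 47 if truncated.

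Both are reproduced. The formula contains no cluster term.

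**2. Dropout alone.**

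- 36 / 0.6 = 60 recruited per arm for 80% power.
- 47 / 0.6 = 78.3, so 79 recruited per arm for 90% power.
- 75 × 0.6 = 45 analysed per arm.

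So 75 falls short of 79 for 90% power before any clustering. For 80% power it leaves 75 − 60 = 15 recruited, or 45 − 36 = 9 analysed, per arm.

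**3. How much clustering that margin covers.** Design effect DE = 1 + (m − 1) × ICC, where m is the number analysed per organisation.

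- With 45 per arm, m = 45 / 4 = 11.25. The largest DE for 80% is 45 / 36 = 1.25, so ICC ≤ 0.25 / 10.25 = 0.024.
- With all 75 per arm, m = 75 / 4 = 18.75. The largest DE for 80% is 75 / 36 = 2.083, so ICC ≤ 1.083 / 17.75 = 0.061. For 90% it is 75 / 47 = 1.596, so ICC ≤ 0.596 / 17.75 = 0.034.

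These limits ignore the small number of clusters.

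**4. Power with eight clusters.** Effective n = n / DE, SE = √(0.41 / effective n), noncentrality = 0.30 / SE. The reference is a t distribution on 8 − 2 = 6 degrees of freedom (critical value 2.447). The normal column uses the same unpooled SE, so it matches the formula that gives 36.

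| Analysed per arm | ICC | DE | Effective n | Power, normal | Power, 6 df |
|---|---|---|---|---|---|
| 45 | 0 | 1.00 | 45.0 | 88% | 75% |
| 45 | 0.02 | 1.21 | 37.3 | 82% | 67% |
| 45 | 0.05 | 1.51 | 29.8 | 72% | 57% |
| 45 | 0.10 | 2.03 | 22.2 | 60% | 46% |
| 75 | 0 | 1.00 | 75.0 | 98% | 92% |
| 75 | 0.02 | 1.36 | 55.4 | 94% | 83% |
| 75 | 0.05 | 1.89 | 39.7 | 84% | 69% |
| 75 | 0.10 | 2.78 | 27.0 | 68% | 53% |

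A beta-binomial simulation with a cluster-level t-test agrees. At the same four ICCs it gives 74%, 66%, 57% and 46% with 11 per organisation, and 92%, 82%, 69% and 53% with 19 per organisation.

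**The case against.** **The article never claims 90% power for 75 per arm.** It lists 36 and 47 and then proposes 75. A reader might infer a promise of 80% to 90% that is broken; the text does not make it. The shortfall against 79 is also small: 47 of 75 would remain at a dropout of 1 − 47/75 = 37.3%, which is close to approximately 40%. This stands.

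**Some room for clustering exists.** A reader might infer that 75 covers dropout and nothing else. At 80% power dropout needs 60, so 15 per arm are left over. This stands, but the article does not say that those 15 are for clustering, or what ICC they would cover.

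**The size of the loss is assumption-driven.** The ICC, the four-against-four split, the equal sizes and the 6 degrees of freedom are not in the article. On a plain design-effect calculation, 80% power survives to an ICC of 0.024 even after the full 40% loss. Power below 80% at every ICC with 45 per arm comes only from the 6-df reference, and the article does not state the degrees of freedom of its multilevel analysis. So a single statement that true power is, say, 50% to 70% is not supported.

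**The 40% may not apply to employment.** Register data continue after questionnaire dropout for those who consent, Table 1 lists Statistics Netherlands for employment, and Trial status says that the primary outcome data come from there. Asking for the register to become the data source would ask for what is largely planned. The article does not give the consent rate, however, and its sample size still applies the 40%.

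**Conclusion.** The point holds as an unquantified cluster allowance: 75 per arm is not shown to be safe. Two parts need no outside figure. The base numbers are for individual randomisation, and 45 analysed per arm is below the plan's own 47 for 90% power, with a design effect of only 1.25 left for 80%.

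The size of the power loss is conditional on the assumed ICC, a four-against-four split, equal organisation sizes and a 6-df reference. On those terms power runs from 75% down to 46% with 45 per arm, and from 92% down to 53% with all 75, for ICC 0 to 0.10. The 80% target is then met only if register retention is high and the ICC is small: 83% at 0.02 and 69% at 0.05 with nobody lost. Unequal organisation sizes would lower these figures further.

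A reader might go on to infer that the trial is definitely underpowered, or that 36 and 47 are miscalculated. Neither follows. The article gives no ICC or register consent rate from which to fix the power, and both base figures match a standard formula.

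**What to change.** Replace the last two sentences of the Sample size section with:

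- the eight randomised organisations and how they split between arms;
- an assumed ICC range (for example 0.02 to 0.10) and the resulting design effects;
- the power for 50% against 20% that follows, on a reference that respects eight clusters, both with the 40% loss and without it.

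Delete the phrase that calls 75 per arm safe. Add one sentence saying that the 40% is questionnaire dropout, and that the powered employment outcome comes from the register data already planned for consenting participants.

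No extra participants or data are needed. Recruitment ended in July 2019, and Trial status says that the researchers cannot see the primary outcome data until three months after the final measurement, so the power can be restated before results are known. The cost is rewording and a less favourable stated power.

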### Statistical analysis

Data will be processed using the statistical software SPSS. Data in this trial will be analyzed on the basis of the statistical principle “intention to treat”, i.e. participants will be analyzed in the arms to which they are assigned. Descriptive analyses will be used to detect significant differences in the baseline characteristics between the intervention group and control group. Longitudinal multilevel analysis will be used to analyze the outcomes. Subgroup analyses will be performed on baseline characteristics and decisional stress at baseline to test whether the groups differ based on baseline characteristics. No additional adjusted analyses will be performed. Baseline characteristics of participants with and without missing values will be examined to test for bias due to missing data. Classical methods of multiple imputations will be used for missing data.

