#### Recruitment of participants

Participants are recruited via the employment specialists working at eight different organizations, and via newspapers and personal letters from the organizations. Inclusion criteria for the study are (1) being unemployed, (2) having sought any treatment (currently or in the past) for MHI, including addiction, by a health professional (e.g. general practitioner (GP), psychologist) and (3) adequate command of the Dutch language, as the intervention and questionnaires are in Dutch. Employment specialists are asked to provide people who meet the inclusion criteria with information about the research and to ask if they are willing to receive more information about the research. If participants give permission to share their contact details with the researchers, they are informed about the research by telephone and the inclusion criteria are checked.

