**Primary outcomes**					
Cost-effectiveness of the intervention	TiC-P EQ-5D-5 L	X	X	X	X
Having employment (yes/no)	Data from Statistics Netherlands^a^ Municipal administration Questions about work, income and benefits	X	X	X	X
Days from baseline until start employment (*n*)		X	X	X	X
Receives social benefits (yes/no)		X	X	X	X
Having other forms of employment (i.e. voluntary work)		X	X	X	X
Decision making about disclosing MHI	DCS Stage of decision making	X	X	X	X

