#### Primary outcomes

The primary outcomes of this study are (1) cost-effectiveness, which will be measured from a societal perspective comparing the intervention with usual care. Healthcare utilization and loss of production will be measured using the Treatment Inventory Costs in Psychiatric Patients (TiC-P), which is a reliable instrument with satisfactory validation [32]. The primary cost-effectiveness outcomes are having employment (yes/no), days from baseline until start employment, receiving social benefits (yes/no) and/or having other forms of employment (i.e. voluntary work, internship). The secondary cost-effectiveness outcome is the EuroQol-5D-5 L, which measures health-related quality of life [33], and (2) decision making about disclosing MHI, measured using the Decisional Conflict Scale, which has adequate test-retest reliability [34], and stage of decision making [35].

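### The primary outcome of days until start of employment is right-censored at 12 months, but the one method stated for all outcomes does not say how people who never start work are handled

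*Protocol article*

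**What the plan says.** Table 1 lists "Days from baseline until start employment" among the primary outcomes and marks it at T0, T1, T2 and T3. The Primary outcomes section names it as one of the primary cost-effectiveness outcomes, and the abstract also lists it as primary.

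Under Recruitment of participants, everyone must be unemployed at entry. Under Study design, follow-up ends at 12 months (T3). Employment data are extracted from municipal and Statistics Netherlands registers from T0 to T3 for those who consent. For participants who consent to the Statistics Netherlands retrieval, collection continues after they stop completing questionnaires.

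The Statistical analysis section names one method: "Longitudinal multilevel analysis will be used to analyze the outcomes". On incomplete data it says "Classical methods of multiple imputations will be used for missing data". It also states intention to treat. It mentions no censoring, no survival or hazard model, and no value or rule for a participant who has not started work by T3.

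The Sample size section takes its rates from a study of another intervention, in which "the average percentage employment was 50% in the intervention group and 20% in the control group".

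**The concern.** The number of days to a first job is one quantity per person. It is known exactly for people who start work by T3. For everyone else it is known only to exceed the follow-up time. Measuring status at four visits does not make it a repeated measure, and at T0 no participant can have a value because all are unemployed.

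A conventional longitudinal multilevel model with days as the response needs a number for each person and has no place for the information that a time is longer than 12 months. The plan does not say where that number comes from for a non-starter, and the possible answers differ greatly:

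- **Drop non-starters.** The comparison is then conditional on a result that arises after randomisation, and it sits badly with the stated intention-to-treat principle.
- **Treat the start date as missing and impute it.** Standard imputation would give a start date within the usual range to someone known not to have started.
- **Set the value to 365 days.** This keeps everyone in and most of the signal, but it is a convention that has to be stated.
- **Analyse as censored time to event.** This uses the data as they are.

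The result on a primary outcome would depend on a choice that the text leaves open.

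**Working it through.** **Inputs.** From the Sample size section: employment 50% and 20%, two-sided 5% significance (sidedness assumed), 75 per group and about 40% dropout, which leaves 75 × 0.60 = 45. From Study design: 12 months of follow-up, taken as 365 days. My assumptions: the 50% and 20% apply at day 365, the hazard is constant within each arm (varied below), and there is no clustering.

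**The plan's own figure.** Two proportions with unpooled variance: n = (z_α/2 + z_β)² × (0.25 + 0.16) / 0.30². At 80% power, n = (1.960 + 0.842)² × 0.41 / 0.09 = 35.8, rounded up to 36 as stated. At 90%, n = (1.960 + 1.282)² × 0.41 / 0.09 = 47.9, against a stated 47. The stated figures are reproduced to within one participant. They concern employment yes/no, not days.

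**Share without a start date.** Intervention 50%, control 80%. Overall 1 − (0.50 + 0.20)/2 = 65%, or 97.5 of 150.

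**Implied effect.** λ = −ln(1 − p)/365 gives 0.001899 and 0.000611 per day. Hazard ratio = ln(0.5)/ln(0.8) = 3.11.

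**Mean days among starters only.** E[T | T ≤ 365] = 1/λ − 365 × (1 − p)/p.
- Intervention: 526.6 − 365.0 = 161.6 days.
- Control: 1635.7 − 1460.0 = 175.7 days.
- Difference: 14.1 days.

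The standard deviations are about 104 and 105 days. With 75 × 0.50 = 37.5 and 75 × 0.20 = 15 starters, SE = √(104²/37.5 + 105²/15) ≈ 32 days. The ratio 14.1/32 = 0.44 gives power of about 7%.

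**Mean days with non-starters set to 365.** p/λ = 263.3 and 327.1 days, a difference of about 64 days.

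**Censored analysis.** Expected events are 75 × (0.50 + 0.20) = 52.5. By Schoenfeld's formula, √52.5/2 × ln(3.11) = 4.11, and 4.11 − 1.96 = 2.15, so power is about 98%. At 45 per arm there are 31.5 events: √31.5/2 × ln(3.11) = 3.18, and power is about 89%.

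**Simulation check.** Individual level, no clustering, Weibull shapes 0.7, 1.0 and 1.5 calibrated to 50% and 20% at day 365; 3,000 runs (1,000 for imputation):

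| Handling of non-starters | Power, 75 per arm | Power, 45 per arm |
|---|---|---|
| Dropped | 6.7–7.5% | 6–7% |
| Imputed (normal model given arm) | 6–9% | 6–8% |
| Set to 365 days | 93–96% | 75–81% |
| Censored (log-rank) | 98% | 86–87% |

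The choice of hazard shape changes little. The handling of non-starters changes almost everything.

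**The case against.** A reader might infer that the plan instructs the analyst to drop or impute non-starters, so that a large effect will be lost. The document does not say that. Imputation is reserved for missing data, and a person known to be out of work at T3 is observed, not missing, on employment yes/no. With consent to the Statistics Netherlands retrieval, that status is recorded even after questionnaire dropout. The intention-to-treat statement also speaks against dropping people. The 7% figure is therefore the result of one possible handling, not of the stated plan. Nor does every analysis of days give a wrong answer, since setting non-starters to 365 days keeps most of the power.

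The stated wording can also cover a sound method. A discrete-time hazard model fitted as a multilevel logistic model on person-periods may fairly be called longitudinal multilevel analysis, and the four marks in Table 1 would suit it. Outcome-specific models are often left to a full protocol or analysis plan, which is not shown.

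The size rests on further assumptions. The article gives no time horizon for the 50% and 20%, which it presents as possible percentages from a study of a different intervention. The 45-per-arm scenario applies questionnaire dropout to an outcome that registers may still supply. All power figures ignore clustering in a trial with eight organisations.

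These objections reduce the size and certainty of the harm. What they leave standing is that the article is not silent: it assigns one method to every outcome, without the exception or censoring rule that this primary outcome needs.

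**Conclusion.** The point holds in a conditional form. A single method is set for all outcomes, including a primary one that is right-censored at T3, and a conventional multilevel model of days does not handle that censoring. If the planning rates apply at 12 months, about 65% of participants have no start date. Depending on how they are handled, power at 75 per arm runs from roughly 7% (dropped or imputed) through 93–96% (set to 365 days) to about 98% (censored). These figures assume constant or Weibull hazards and no clustering. The low end is a worst case that the text permits but does not prescribe.

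Only this outcome is affected. Employment yes/no, on which the sample size rests, can be analysed as planned. This should be fixed, but it does not undermine the trial.

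**What to change.** Add to the Statistical analysis section, or to the analysis plan:

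- Days until start of employment is analysed as time from baseline to first paid employment, using register dates.
- Follow-up is censored at T3 or at the end of register coverage, whichever comes first.
- Clustering by organisation is in the model, through a Cox model with shared frailty or a discrete-time multilevel hazard model. If the latter is what the present sentence means, saying so settles the point.
- Known non-employment at T3 is censoring and is not imputed.

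The cost is a change of wording and slightly more analysis work. Employment data from T0 to T3 are already to be extracted. The Trial status section says the researchers have no access to the primary outcome data until 3 months after the final measurement, so on the article's account the rule can be fixed before those data are seen.

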### Objective and research questions

An RCT is conducted to examine the effects of an innovative intervention based on the English CORAL decision aid [23], which has been adapted to the Dutch context and embedded in an intervention for unemployed people with MHI and workplace stigma-awareness training especially designed for employment specialists. Furthermore, factors that facilitate finding employment and factors that hamper this will be studied. The primary research questions of this study are:
Does the intervention more often lead to finding and retaining paid employment for unemployed people with mental health problems, compared to usual guidance in municipal practice, controlled for other factors (e.g. mental health and stigma and discrimination)?Is the intervention cost-effective from a societal perspective (including reintegration costs and healthcare costs)?For whom, under which circumstances and in what way does the intervention work best or less well, and why?

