## Trial status

The study is registered under trial registration number NL7798 (registered 4 June 2019 - retrospectively registered; https://www.trialregister.nl/trial/7798). Participant recruitment started in April 2018 and ended in July 2019. Data collection will end in July 2020. The data gathering is in progress. According to the municipalities, there were difficulties in engaging and scheduling appointments with the target group, which delayed the submission of the study protocol paper. Priority was given to the hundreds of face-to-face meetings that need to be scheduled for data gathering. However, the researchers have no access to the primary outcome measures of the study until 3 months after the final measurement, as the primary outcome data will be retrieved from a different organization (i.e. Statistics Netherlands, an organization with very strict data security) 3 months after the end of the data gathering process.

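### The primary question promises an effect controlled for other factors, but the analysis section names no covariates and rules out additional adjusted analyses, in a design open to selective recruitment

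*Protocol article*

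**What the plan says.** All of this is in the protocol article.

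- **Objective and research questions.** The first primary question asks whether the intervention more often leads to finding and keeping paid work, "compared to usual guidance in municipal practice, controlled for other factors (e.g. mental health and stigma and discrimination").
- **Statistical analysis.** Outcomes go into a longitudinal multilevel analysis under intention to treat, with no covariate named. On baseline data: "Descriptive analyses will be used to detect significant differences in the baseline characteristics between the intervention group and control group". No action is stated if a difference is found. After the sentence on subgroup analyses comes "No additional adjusted analyses will be performed".
- **Randomization of employment specialists (ES).** "All 72 participating employment specialists were recruited between November 2017 and March 2018 from eight participating organizations". Then: "After including all employment specialists, the organizations were randomly allocated to either the intervention or control condition, using SPSS software". Neither specialists nor researchers can be masked.
- **Recruitment of participants.** "Employment specialists are asked to provide people who meet the inclusion criteria with information about the research". Newspapers and letters from the organisations are further routes, and the researchers check eligibility by telephone.
- **Trial status.** "Participant recruitment started in April 2018 and ended in July 2019".
- **Strengths and limitations.** The article concedes that recruiting through specialists may bring selection bias.

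**The concern.** Read literally, the analysis section leaves the first primary question unanswerable as posed: the question wants a controlled effect, and the analysis describes only an uncontrolled one.

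The design makes the mismatch more than editorial. In a cluster trial, randomisation protects the comparison of participants only if recruitment does not depend on the arm. Here the people who approach candidates know their arm. In the intervention arm they also receive training on stigma and disclosure from the start of the study, in three meetings within six months (Intervention/training-based care). Such training could change whom they recognise as eligible and whom they approach. If it does, the unadjusted contrast mixes the effect of the intervention with a difference in who was recruited. Intention to treat does not repair that, because the difference arises at entry. An unadjusted model also gives up precision from prognostic data that Table 1 shows are collected at T0.

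The research question has a weakness of its own. Mental health, stigma and discrimination are secondary outcomes measured at every visit, and the question does not say that only baseline values are meant. Control for follow-up values could remove part of the effect under study.

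**Working it through.** **1. The plan's own figure, for scale.** The point does not rest on a figure in the plan, but the planned effect and group size set the scale. Sample size assumes 50% against 20% employment, a difference of 30 points. With unpooled variance and two-sided 5%:

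n = (z_a + z_b)² × [p1(1−p1) + p2(1−p2)] / (p1−p2)²

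- 80% power: (1.960 + 0.842)² × (0.25 + 0.16) / 0.09 = 35.76, so 36, as stated.
- 90% power: 47.87, against 47 stated. This has no bearing here.

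The plan recruits 75 per group. After 40% dropout, 75 × 0.6 = 45 remain.

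**2. Question against analysis.** The question names mental health, stigma and discrimination as factors to control for. The analysis section names none of them, and no other covariate, and closes the matter with the sentence quoted. Subgroup analyses are planned, but they do not adjust the main effect.

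**3. Order of events.** Specialists were recruited from November 2017 to March 2018, organisations were allocated once all specialists were in, and participants were recruited from April 2018. The allocation date is not printed. That allocation came before participant recruitment is an inference from these dates.

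**4. What the baseline test can detect.** Take a binary baseline factor, 75 per arm, two-sided 5%, clustering ignored:

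power = Φ{[d − 1.96 √(2 p̄(1−p̄)/n)] / √([p1(1−p1) + p2(1−p2)]/n)}

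| Shares by arm | Calculation | Power |
|---|---|---|
| 55% vs 45% | (0.10 − 0.160) / 0.0812 = −0.74 | about 23% |
| 60% vs 40% | (0.20 − 0.160) / 0.0800 = 0.50 | about 69% |
| 65% vs 35% | (0.30 − 0.160) / 0.0779 = 1.80 | about 96% |

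The test is weak for a 10-point imbalance, moderate for 20 and good for 30. In every case the plan says nothing about what happens next.

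**5. Illustration of size (all inputs assumed).** Suppose the intervention has no effect, and 12-month employment is 30% in better-prognosis and 10% in worse-prognosis participants. The spurious difference is the difference in shares × (0.30 − 0.10):

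- 10 points: 0.10 × 0.20 = 2 percentage points
- 20 points: 0.20 × 0.20 = 4 percentage points
- 30 points: 0.30 × 0.20 = 6 percentage points

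For shares of 60% and 40%, expected employment is 0.6 × 0.30 + 0.4 × 0.10 = 22% against 0.4 × 0.30 + 0.6 × 0.10 = 18%. With 75 per arm the standard error is √[(0.22 × 0.78 + 0.18 × 0.82)/75] = 0.0652. The ratio is 0.04 / 0.0652 = 0.61, so a nominal 5% test rejects about 9% of the time, clustering ignored. If the imbalance comes from selective recruitment, a larger sample does not remove it.

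**The case against.** The strongest reply is that the sentence is read too hard. It speaks of *additional* adjusted analyses, after the main model and the subgroup analyses, and may mean none beyond covariates already in that model. The research question supports this reading, and an article may leave a covariate list to the full analysis plan. This stands in part: a reader might infer a proven ban on all adjustment, and the text does not establish one. But no covariate is named anywhere, so the two sections must still be reconciled, and the sentence as printed points the wrong way.

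Further objections limit the point:

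- **Recruitment.** A reader might infer that specialists alone choose the participants. They do not: there are newspapers and letters, and researchers check eligibility. The researchers are unmasked too, so their check does not remove the risk.
- **Eight clusters.** Chance differences between organisations add variance, which a multilevel model can address. They are not systematic bias. Imbalance with eight clusters is likely, not certain.
- **Size.** The 2 to 6 points rest wholly on assumed inputs and are small beside the planned 30.
- **Baseline testing.** It is not powerless at a 20-point imbalance. The fair criticism is the missing consequence.
- **Follow-up values.** Nothing in the article says that they will be controlled for. The wording merely fails to exclude it.

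**Conclusion.** The conflict between the research question and the analysis section is real and should be resolved before analysis. It has substance because recruitment is largely in unmasked hands, apparently after allocation, with few clusters and an admitted risk of selection, and because the only safeguard in the text is a significance search that leads nowhere.

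The documents do not show that selective recruitment occurred, in which direction, or how large its effect was. The 2 to 6 points show what a moderate arm-dependent imbalance could do and are not an estimate for this trial. Nor should a reader infer that adjustment would cure the problem: selection on unmeasured traits, such as motivation, would remain. Adjusting for baseline variables reduces bias from measured factors, improves precision, and makes the analysis answer the question asked.

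**What to change.** 1. Delete the sentence on additional adjusted analyses. Make the adjusted multilevel model primary and report the unadjusted model as a sensitivity analysis.
2. Pre-specify a short set of T0 covariates, chosen from age, gender, education, history of mental ill-health, and baseline mental health and stigma. Include baseline stigma only if specialist training cannot have altered it before T0. Any factor named in the research question but left out of the model should be dropped from its wording. Duration of benefits is a poor candidate: Study design describes it only as register data for consenting participants.
3. Fix the list before the registry outcomes are released. Trial status puts that three months after the end of data gathering, so at the time of the article it was still possible. The questionnaires also ask about work, so the list should not be chosen after looking at those answers by arm.
4. State in the research question that only baseline values are controlled for.
5. Replace baseline significance testing with a descriptive table by arm and organisation.

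The cost is a change of wording, since these variables are already collected at T0. Eight organisations and 150 participants allow few covariates. An adjusted odds ratio is a different quantity from the unadjusted one, so a standardised risk difference should be given beside it.
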